## Abstract

**Background:**

Social distancing is a crucial intervention to slow down person-to-person transmission of COVID-19. However, social distancing has negative consequences, including increases in depression and anxiety. Digital interventions, such as text messaging, can provide accessible support on a population-wide scale. We developed text messages in English and Spanish to help individuals manage their depressive mood and anxiety during the COVID-19 pandemic.

**Objective:**

In a two-arm randomized controlled trial, we aim to examine the effect of our 60-day text messaging intervention. Additionally, we aim to assess whether the use of machine learning to adapt the messaging frequency and content improves the effectiveness of the intervention. Finally, we will examine the differences in daily mood ratings between the message categories and time windows.

**Methods:**

The messages were designed within two different categories: behavioral activation and coping skills. Participants will be randomized into (1) a random messaging arm, where message category and timing will be chosen with equal probabilities, and (2) a reinforcement learning arm, with a learned decision mechanism for choosing the messages. Participants in both arms will receive one message per day within three different time windows and will be asked to provide their mood rating 3 hours later. We will compare self-reported daily mood ratings; self-reported depression, using the 8-item Patient Health Questionnaire; and self-reported anxiety, using the 7-item Generalized Anxiety Disorder scale at baseline and at intervention completion.

**Results:**

The Committee for the Protection of Human Subjects at the University of California Berkeley approved this study in April 2020 (No. 2020-04-13162). Data collection began in April 2020 and will run to April 2021. As of August 24, 2020, we have enrolled 229 participants. We plan to submit manuscripts describing the main results of the trial and results from the microrandomized trial for publication in peer-reviewed journals and for presentations at national and international scientific meetings.

**Conclusions:**

Results will contribute to our knowledge of effective psychological tools to alleviate the negative effects of social distancing and the benefit of using machine learning to personalize digital mental health interventions.

**Trial Registration:**

ClinicalTrials.gov NCT04473599; https://clinicaltrials.gov/ct2/show/NCT04473599

**International Registered Report Identifier (IRRID):**

DERR1-10.2196/23592

## Introduction

### Background

The current COVID-19 pandemic not only poses a large threat to physical health but also has detrimental consequences for mental health. Social distancing is a crucial intervention to slow down person-to-person transmission of this infectious disease. However, culminating research shows that it also has unintended consequences for large groups of the population: increased anxiety, depression, and stress [1,2]; decreased physical activity [3,4]; and lower sleep quality [5]. In the United States, vulnerable populations from low-income backgrounds, people of color, and Spanish speakers are more likely to work in jobs where they are at higher risk of contracting COVID-19 [6]. In part because of this, these groups experience disproportionately worse mental health outcomes [6,7].

The current situation calls for new and innovative digital methods to reach vulnerable populations [8]. Text-messaging interventions, which can be implemented during social distancing, have previously demonstrated effectiveness in behavioral health promotion and disease management [9]. They are also suitable for low–digital literacy populations and underserved groups [10]. For instance, our own Health Insurance Portability and Accountability Act (HIPAA)-approved texting platform, HealthySMS, has shown high acceptability and engagement among low-income English and Spanish speakers in California [11-13].

We developed text messages based on cognitive behavioral therapy to help people cope with the stress and anxiety of COVID-19 social distancing. Messages are developed within two different categories: behavioral activation (BA) [14] and other skills, more typical of psychoeducation for improving mood [15]. BA messages include prompts to increase BA and decrease avoidance of anxiety-inducing situations. Other skills focused on changing thinking patterns and tips about sleep, self-care, and breathing exercises; see examples of messages in Table 1. We will distribute this text messaging system to a wide group of individuals in the United States via social media advertisements. Further, we designed these messages both in English and in Spanish, enabling the program to reach a diverse group of people. Mobile health interventions are less often designed for Spanish speakers.

### Objective

The main purpose of this study, which is called the StayWell at Home study, is to examine whether automated text messages will improve depression and anxiety symptoms and enhance positive mood. Additionally, we will compare the effectiveness of sending messages on a random schedule using a microrandomized trial (MRT) design [16], further referred to as *uniform random* (UR), or sending messages via a *reinforcement learning* (RL) algorithm on the overall change in depression and anxiety symptoms and daily mood during the 60-day study. Finally, within the microrandomized group, we will examine which types of text messages are more effective in helping people increase their positive mood. We will examine the hypotheses discussed in the following two sections.

### Primary Analysis

We hypothesize that participants will show improvements in depression symptoms, measured using the 8-item Patient Health Questionnaire (PHQ-8); anxiety symptoms, measured using the 7-item Generalized Anxiety Disorder (GAD-7) scale; and daily mood during the 60-day study. We will conduct a pre-post comparison among all participants.

We hypothesize that the participants in the group receiving RL will have a greater decrease in depressive symptoms and anxiety and a greater daily increase in mood ratings during the 60-day study than participants in the UR group (ie, randomized design).

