### Measures

For our primary outcomes, we will administer a survey at baseline and at 60-day follow-up, which includes the PHQ-8 [19] and GAD-7 [20]. In addition to these questionnaires, we will also ask open-ended questions to assess how participants are impacted by COVID-19. Questionnaire data will be stored on UC Berkeley’s Qualtrics platform. Our secondary outcome, daily mood ratings, will be collected via text message on a daily basis and stored on the HealthySMS platform. The project coordinator and research assistants will be responsible for managing patient data collection. Once data from all participants are collected, they will be stored on UC Berkeley’s Secure Box, a secure cloud-hosted platform. See Table 1 [21,22] for all included questionnaires and timing of their administration.

**Table 1 table1:** Questionnaires included in the StayWell at Home study and timing of administration.

Questionnaire^a^	Baseline	Follow-up
PHQ-8 (8-item Patient Health Questionnaire)^b^	X^c^	X
GAD-7 (7-item Generalized Anxiety Disorder) scale^b^	X	X
COVID-19 questions	X	X
System Usability Scale^d^	N/A^e^	X

^a^The measures were taken from validated questionnaires in English and Spanish.

^b^The PHQ-8 depression scale and the GAD-7 anxiety scale were not modified.

^c^X indicates that the measure was administered at this time point.

^d^The System Usability Scale [21] was modified to decrease literacy levels, using the Flesch-Kincaid readability test [22].

^e^N/A: not applicable; the measure was not administered at this time point.

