### Power Analysis

We will perform sample size calculation at the usual 80% power at 5% level of significance.

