#### Primary Analysis

The Cohen methods [30] were used to calculate sample sizes for primary hypotheses. At a medium standardized effect size (ie, Cohen *d*=0.5), a total sample size of 64 is required to detect an improvement of either the depression or anxiety score from baseline to 60-day follow-up, and a sample size of 128 to detect differences between the UR and RL groups.

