#### Secondary Analyses

Using the GEE-based sample size calculation method [31,32] with a small standardized effect size (ie, Cohen *d*=0.2), with the correlation coefficients of 0.2 and 0.4 among the daily mood rating improvements compared to baseline, sample sizes of 84 and 161 are required to detect a group effect for either the UR or RL group, respectively, randomly allocated at baseline. Assuming 15% of the participants will drop out before the end of the study, a sample size of 190 is required for each group.

At a small standardized effect size (ie, Cohen *d*=0.1), with a constant trend of intervention effect over days, sample sizes of 55 and 76 are required to detect the average daily causal effects of message and time window, respectively, for the UR intervention group, using the WCLS-based sample size calculation method proposed by Xu et al under the multilevel MRT design [33]. Assuming each participant has an expected 70% response rate to the sent messages and 15% of the participants are expected drop off before the end of the study, a sample size of 126 is recommended for the UR group. 

Since our primary aim is to detect differences between the UR and RL groups for depression and anxiety scores, we aimed to include at least 128 participants. However, since our goal is also to provide a service during this unprecedented COVID-19 pandemic, we will continue to make the program available and recruit participants until at least April 2021 or for as long as funding allows.

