### Limitations

There are disadvantages to fully online recruitment. For instance, participants may perceive a lack of connection to the research without contact with the researcher and, therefore, show lower engagement [39]. Furthermore, online recruitment comes with risks of fraudulent activity. In addition, our monetary incentive may lead to a selection of a sample mostly motivated by financial incentives. We aimed to minimize this potential bias by only providing the reimbursement at the end of the study. We also aimed to design a messaging bank with content relevant for a broad demographic group. Thus, the content might not be adequately tailored toward specific subgroups (eg, people with chronic physical diseases or severe mental illness). Finally, we use a multilevel MRT design as opposed to contrasting sending a message with not sending a message, which is a more common design. However, by using this design, we will not be able to assess the pooled effectiveness of sending any message versus no message.

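### The stated main purpose, whether the messages improve depression and anxiety, rests on a pre-post test with no unmessaged group, and the document contradicts itself on which comparison is primary and on the status of mood

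*Protocol article*

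**What the plan says.** **Aim.** The Objective section says that the main purpose "is to examine whether automated text messages will improve depression and anxiety symptoms and enhance positive mood". It introduces the comparison of reinforcement learning (RL) with uniform random (UR) messaging as an additional question. The Discussion (Overview) and the Conclusions repeat the aim of establishing what the messages do.

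**Analysis serving that aim.** The Introduction's Primary Analysis hypothesizes improvement in PHQ-8, GAD-7 and daily mood, and adds: "We will conduct a pre-post comparison among all participants". Design lists this as a separate pre-post design for depression and anxiety. The Statistical Analysis Plan (Primary Analysis) carries it out with paired t tests on PHQ-8 and GAD-7.

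**Comparator.** Under Reinforcement Learning Policy, the two arms get the same messages and differ only in how type and timing are selected. Limitations, discussing the multilevel microrandomized design, says "we will not be able to assess the pooled effectiveness of sending any message versus no message".

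**Hierarchy.** The closing paragraph of Power Analysis (Secondary Analyses) reads: "Since our primary aim is to detect differences between the UR and RL groups for depression and anxiety scores". Measures has "Our secondary outcome, daily mood ratings", and Power Analysis sizes the mood comparison under its secondary heading. Yet mood is among the primary hypotheses in the Introduction, and its between-arm analysis stands under Primary Analysis in the Statistical Analysis Plan.

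**Level.** Power Analysis: "We will perform sample size calculation at the usual 80% power at 5% level of significance".

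**The concern.** Whether messages improve symptoms is a causal question. A paired test in people who all receive messages answers a different one: did scores change over 60 days? Enrolment runs from April 2020 to April 2021, and the Background section itself says that social distancing raises depression and anxiety. Symptoms can therefore move in either direction for reasons unrelated to the messages, and the paired test assigns all of that movement to the before-after contrast. A significant result could be reported as evidence that the messages work when the design cannot show it.

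The conflicting labels add a second risk. With two candidates for the primary comparison, and mood both primary and secondary, which result leads the report can be settled after the data are seen. Within RL versus UR there are also two co-primary scores, and the sample size was planned as if there were one.

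**Working it through.** **Inputs from the protocol article:** 5% level and 80% power (Power Analysis); d = 0.5 ("At a medium standardized effect size", Power Analysis, Primary Analysis); 128 in total for RL versus UR; 1:1 allocation (Design); 15% dropout (stated for the secondary calculations only); 229 enrolled by August 24, 2020 (Results).

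**Assumed, because the document gives no figure:** two-sided tests; background change of 0.1 to 0.3 SD of the change score; correlation of 0.5 to 0.8 between the PHQ-8 and GAD-7 test statistics; 15% dropout applied to the primary comparison.

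**1. Reproduce the stated 128.** Two-sample t test, d = 0.5, two-sided alpha 0.05, 80% power: 63.8, so 64 per arm and 128 in total. (The normal approximation, n = 2(1.960 + 0.842)²/0.5², gives 63 per arm.) The figure thus reproduces with the full, unadjusted 5% spent on a single endpoint. At alpha 0.025 the requirement is 78 per arm, 156 in total.

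**2. Pre-post test with zero message effect.** The paired t statistic has noncentrality δ√n, where δ is the background improvement in SDs of the change score. For n = 128 and δ = 0.2 this is 0.2 × 11.31 = 2.26. The probability of a significant result at two-sided 5% is:

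| n | δ = 0.1 | δ = 0.2 | δ = 0.3 |
|---|---|---|---|
| 64 | 12% | 35% | 66% |
| 128 | 20% | 61% | 92% |
| 229 | 33% | 85% | 99.5% |

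The n = 64 row is the size planned for this test ("a total sample size of 64 is required to detect an improvement of either the depression or anxiety score from baseline to 60-day follow-up"). The probability rises with n, so continued recruitment makes the problem larger. Background worsening of similar size would work against a true benefit.

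**3. Two endpoints for RL versus UR, each at two-sided 5%.** The chance of at least one false positive is 1 − 0.95² = 9.75% if the endpoints are independent, 9.1% at correlation 0.5 and 7.8% at 0.8. Counting only false findings that RL is better, it is 4.5% at 0.5 and 3.9% at 0.8, against 2.5% for one test.

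**4. Power with Holm.** The smaller p value is tested at 0.05/2 = 0.025. At 64 per arm and d = 0.5, per-endpoint power falls from 80% to 71%. With 229 × 0.85 ≈ 195 evaluable, it is 89%. The 156 evaluable needed for 80% power become 156/0.85 = 183.5, so 184 enrolled.

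**5. Labels side by side.**

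| Item | Primary in | Not primary in |
|---|---|---|
| RL versus UR | Introduction, Primary Analysis; Power Analysis, last paragraph (primary aim) | Objective (additional) |
| Daily mood | Introduction, Primary Analysis; Statistical Analysis Plan, Primary Analysis | Measures; Power Analysis, Secondary Analyses |

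**The case against.** The strongest reply is that the pre-post analysis is openly labelled as such, that its hypothesis says only that participants will improve, and that a paired t test is a proper test of change. That is right as far as it goes. A reader might infer that the hypothesis itself credits the messages; it does not. The attribution comes from Objective, Discussion (Overview) and Conclusions, which have no other analysis behind them.

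A reader might also take the Limitations sentence as disowning the pre-post test. It concerns the multilevel microrandomized design and bears on the pre-post test only by implication. The implication holds, because no participant goes without messages.

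A third tempting reading is six primary tests, each at 5%, with familywise error up to 26.5%. The document does not support it. The Statistical Analysis Plan lists five tests, since mood has no paired test. The 5% is stated for the sample size calculation, and a rule for multiplicity may stand in a fuller plan that is not shown. The pre-post and between-arm tests also answer different questions, so pooling them is a choice. Only the two-endpoint figure for RL versus UR is used here, and it is conditional.

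Regression to the mean should not be pressed: there is no symptom threshold for entry, and the recruitment text describes targeting low-income, vulnerable groups rather than distressed people. Nor is the size of background change documented. At 0.10 SD the test would be significant 28% of the time with 195 evaluable and 18% with 109 (128 less 15%), so no single figure should be quoted without its range.

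**Conclusion.** The point stands in two firm parts and one conditional part.

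- **Firm:** the stated main purpose cannot be met by the analysis assigned to it. No sample size and no separate analysis plan can supply the missing unmessaged group. The size depends on assumed background change: at n = 128, a 20% to 92% chance of a significant result with no message effect, for 0.1 to 0.3 SD of improvement.
- **Firm:** the sections contradict each other on the primary comparison and on the status of mood. This needs no assumption.
- **Conditional:** if PHQ-8 and GAD-7 are each tested at 5%, the familywise error for RL versus UR is about 8-9% two-sided, or about 4-4.5% for a false finding that RL is better.

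The randomized RL versus UR comparison itself is not undermined by the missing unmessaged group.

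**What to change.** 1. Report the pre-post result as mean change over time with a 95% CI and no efficacy wording. Reword Objective, Discussion (Overview) and Conclusions to match.
2. Name RL versus UR on PHQ-8 and GAD-7 as the confirmatory comparison, identically in Objective and Power Analysis, using Holm at an overall two-sided 5%.
3. List daily mood as secondary throughout, including the Introduction's Primary Analysis and the Statistical Analysis Plan.

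Randomization and data collection stay as they are. The cost is rewording and some power: at the first Holm step, per-endpoint power for d = 0.5 falls from 80% to 71% at 128 evaluable, but is about 89% at 195 evaluable. The 229 already enrolled exceed the 184 needed for 80% power at that step with 15% dropout.

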### Secondary Analysis

We hypothesize that we will find differential effects on mood ratings for the two categories of messages and different timings (ie, microrandomized design).

## Methods

### Design

This study has various designs: (1) a pre-post comparison, in which we assess changes in depression and anxiety for all patients before and after the intervention; (2) a randomized controlled trial with two groups, RL and UR; and (3) an MRT, only within the UR group.

Randomization will be performed as block randomization with a 1:1 allocation. Participants will be automatically randomized into groups through our secure server during onboarding of the study, ensuring allocation concealment. Participants will be informed of the nature and frequency of the messages they will be receiving. They will be blinded to their group randomization. Further, if messages are not sent out appropriately, research assistants will contact the developer to address errors (eg, when individuals do not receive messages, or they receive messages out of the specific time bounds). Throughout the study, the researchers will check whether the randomization of messages is functioning adequately approximately once every two months. The necessity of these steps makes it infeasible to blind the researchers. Microrandomization will happen automatically on a daily basis through our secure server. We used the SPIRIT (Standard Protocol Items: Recommendations for Interventional Trials) checklist when writing this protocol [17]. Figure 1 shows our study design.

**Figure 1 figure1:**
[figure not shown]
StayWell at Home study design.

### Recruitment

This is a fully remote trial. We will recruit on social media platforms, such as Facebook, Twitter, and Craigslist, and through university websites (ie, University of California [UC] Berkeley and UC San Francisco). Our posts and ads will be designed by the research team to target low-income, vulnerable populations across the United States. We will utilize the *detailed targeting* feature on Facebook to select the group of people to whom we want to show our ads. We will recruit in both English and Spanish.

The Facebook posts and ads will be informed by user-centered design (UCD) methods, including implementation of user personas in recruitment efforts. User personas, a common UCD tool [18], consist of fictional characters that represent our target populations. The user personas will include English speakers and Spanish speakers of various demographic groups. Each ad will contain a title and picture, followed by a reason for participating in the study and enrollment details. We will rely on Facebook’s built-in algorithms to present the most relevant ad version to each viewer.

### Inclusion Criteria

We will include adults 18 years or over who have a functioning mobile phone and who speak English and/or Spanish. We will exclude participants who use an online text messaging app, as this is more prone to online scams and fraud (eg, individuals creating fake accounts to receive reimbursements). Through targeted ads, we will make concerted efforts to recruit vulnerable populations, such as low-income individuals and people of color, who are disproportionately impacted by COVID-19 in the United States.

### Measures

For our primary outcomes, we will administer a survey at baseline and at 60-day follow-up, which includes the PHQ-8 [19] and GAD-7 [20]. In addition to these questionnaires, we will also ask open-ended questions to assess how participants are impacted by COVID-19. Questionnaire data will be stored on UC Berkeley’s Qualtrics platform. Our secondary outcome, daily mood ratings, will be collected via text message on a daily basis and stored on the HealthySMS platform. The project coordinator and research assistants will be responsible for managing patient data collection. Once data from all participants are collected, they will be stored on UC Berkeley’s Secure Box, a secure cloud-hosted platform. See Table 1 [21,22] for all included questionnaires and timing of their administration.

**Table 1 table1:** Questionnaires included in the StayWell at Home study and timing of administration.

Questionnaire^a^	Baseline	Follow-up
PHQ-8 (8-item Patient Health Questionnaire)^b^	X^c^	X
GAD-7 (7-item Generalized Anxiety Disorder) scale^b^	X	X
COVID-19 questions	X	X
System Usability Scale^d^	N/A^e^	X

^a^The measures were taken from validated questionnaires in English and Spanish.

^b^The PHQ-8 depression scale and the GAD-7 anxiety scale were not modified.

^c^X indicates that the measure was administered at this time point.

^d^The System Usability Scale [21] was modified to decrease literacy levels, using the Flesch-Kincaid readability test [22].

^e^N/A: not applicable; the measure was not administered at this time point.

